## Abstract

**Background:**

South Africa recently phased out access to free formula milk in the public sector in support of breastfeeding for women living with HIV. Few women living with HIV in South Africa choose breastfeeding and among those who do, many stop breastfeeding early. We sought to explore the feasibility of using mobile phone text messaging coupled with motivational interviewing to enhance adherence to breastfeeding practices.

**Methods and design:**

A randomized, parallel group, single-center pilot trial. Electronic sequence generation and random allocation will be done centrally. Women of low socioeconomic status, from Cape Town, South Africa will be randomly assigned within 24 h of giving birth at a primary healthcare clinic to a structured weekly text message plus motivational interviewing and usual standard of care, using a permutation of different block sizes. Criteria for feasibility success will include: five participants recruited per week (over 12 weeks), about 75% of all eligible participants consent for study participation, complete evaluation of outcomes in at least 70% of all recruited participants, breastfeeding adherence rates of at least 70% in the intervention group, six months after delivery. Participants will be evaluated soon after giving birth and post-delivery at weeks 2, 6, 10, and 24. Primary analysis will follow the “intention-to-treat” principle. Sub-group analysis will be used to assess sub-group effects.

**Discussion:**

This pilot trial will evaluate the feasibility of conducting a larger trial on communication and support approaches to improve adherence to breastfeeding by HIV-infected women. Text messaging and motivational interviewing are simple interventions which may allow participants to access personalized adherence advice and support.

**Trial registration:**

ClinicalTrials.gov: NCT02949713. Registered on 26 October 2016; Pan African Clinical Trial Registry PACTR201611001855404. Registered on 8 November 2016.

**Electronic supplementary material:**

The online version of this article (doi:10.1186/s13063-017-2079-0) contains supplementary material, which is available to authorized users.

## Background

Since the detection of HIV transmission through breastfeeding, developed countries recommend formula feeding for HIV-infected women [1]. In resource-limited settings, where child mortality is mainly due to diarrhea, pneumonia, and malnutrition, the effectiveness of antiretroviral treatment (ART) in reducing the risk of HIV transmission through breastfeeding has largely resolved the dilemma on how HIV-infected women should feed their infants [2–4]. In such settings, the World Health Organization (WHO) recommends at least 12 months of breastfeeding with infant or maternal ART [5, 6]. Breastfeeding improves child health and development [7–17].

South Africa, a country with a high prevalence of HIV, recently phased out access to free formula milk in the public sector in support of breastfeeding for women living with HIV. Despite the evidence showing reduced risk of infants dying from infections when breastfed, especially in high HIV prevalence settings, breastfeeding rates remain low with challenges to promote breastfeeding by HIV-infected women [7–10]. We conducted a prospective cohort study in South Africa, when the Western Cape prevention of mother-to-child transmission program was phasing out access to free formula milk [18]. We found that few HIV-infected women chose to breastfeed; among those who did, many (50%) switched to formula feeding early (approximately four months following delivery) [18]. Developing simple interventions to promote and sustain continued breastfeeding by women is a public health priority.

Mobile phone text messaging (mHealth) is a simple, low-cost intervention that can promote health behavior change [19, 20]. Increasing mobile phone use in Africa stimulated research efforts on how to leverage mobile phones as a communication tool in healthcare. Text messaging improves adherence to medication among HIV-infected, diabetes, and tuberculosis patients [21–23]. Text messaging not only improves adherence to ART, but also reduces viral load and treatment interruptions [23, 24]. These trials suggest that specific characteristics of the text messages such as interactivity, timing, and content influence text messaging efficacy. Interactive weekly text messaging was superior to interactive daily text messaging [25]. One similarity between adherence to ART and infant feeding practice is that both have a strong behavioral modification aspect: HIV-infected people have to take medication to control the disease while breastfeeding women must modify their feeding practices to improve the health outcomes of their infants. These similarities justify applying information about text messaging from ART adherence studies to infant feeding practices.

Current research suggests that combining a number of approaches is more likely to influence behavior change than an individual approach [26, 27]. Home visits by community health workers and motivational interviewing are interventions known to influence behavior change [28, 29]. However, the former requires considerable human resources and may not be feasible in low-resource settings where the number of healthcare workers is constrained. Patient-centered approaches for negotiating behavior change outperform approaches that instruct patients to change behavior through providing advice [30, 31]. Motivational interviewing is a patient-centered approach that is less coercive and explores the patient’s readiness to change behavior and support the person’s commitment to do so in the preferred direction [32, 33]. Motivational interviewing was of benefit across many health problems, including HIV viral load suppression, body weight, and alcohol and tobacco use [34]. Motivational interviewing is more effective when combined with other interventions [35]. Little is known about the effect of mobile phone text messaging added to motivational interviewing on supporting adherence to breastfeeding among HIV-infected women.

This pilot trial protocol was written following the standard protocol items recommendations for interventional trials (SPIRIT) guidelines (see Additional file 1 SPIRIT checklist) [36].

## Methods and design

### Study design

We will assess the feasibility of the intervention at a single site: mother–infant pairs will be randomly assigned to interactive mobile phone text messaging plus motivational interviewing or usual standard of care (see Fig. 1).

**Fig. 1 Fig1:**
[figure not shown]
Spirit figure of the pilot trial

## Randomization scheme

Participants will be randomly assigned to study groups using a permuted block method. The randomization sequence will be generated using a random number generating program, with a 1:1 allocation ratio with blocks of different sizes to ensure a balanced allocation. Block sizes will be randomly permuted. Electronic sequence generation and random allocation will be done centrally. Women meeting inclusion criteria who consent to participate will be enrolled and immediately assigned a study arm in sequential order. The principal investigator will coordinate the procedures. Only data analysts will be blinded to participant allocation.

## Setting and study population

Women from peri-urban informal settlements will be invited to participate within 24 h of giving birth at a primary healthcare clinic in Cape Town, South Africa.

### Inclusion criteria

HIV-infected mothers will be eligible for inclusion if they initiate breastfeeding within 24 h of giving birth, are on ART, are 18 years or older, own a mobile phone, and their infants are judged to be in good health (ready to be discharged soon after delivery).

### Exclusion criteria

Participants will be excluded if inclusion criteria are not met or if viral load is > 400 copies/mL, if they initiate formula feeding within 24 h of giving birth, gave birth to more than one infant, or if the birth weight is < 2000 g or the gestational age is < 36 weeks. High viral load, multiple birth, and low birth weight are associated with sub-optimal infant feeding practices and poor infant outcomes.

## Study interventions

All women and their infants, irrespective of their study assignments, will receive health services and treatment according to the respective provincial guidelines applicable in the sector during the study. No deviation from existing guidelines will be caused by taking part in this study. Participants will be evaluated soon after giving birth and post delivery until cessation of breastfeeding or until end of the study. Children will be tested for HIV infection at time points already in routine practice (i.e. at birth and ten weeks). We will extract information on the children’s HIV status from the clinical and laboratory records.

### Mobile phone text messaging

Consented new mothers will register their phone numbers into an automated text message (SMS) software (provided by WelTel.org). The first SMS will be sent within the first week following delivery. Every Monday morning, a text message will be sent to women in the intervention group encouraging them to exclusively breastfeed and inquire if they have any problems breastfeeding their infants. Participants will be asked to respond by text within 48 h, indicating that they either do not have a problem or they have a problem and require help. Participants may also use the free ‘call back’ function to request a call from the nurse for complex issues or if cost or literacy is a problem. The research nurse will review all the responses and then follow-up and provide triage to any participants who indicate a problem or call participants who fail to respond within 48 h. To preserve confidentiality, the content of the text messages will not be related to the woman’s HIV status. Participants will be briefly trained on use of the phone and the text messaging protocol.

### Motivational interviewing

In addition to text messaging, women will have individual motivational interviews post delivery at weeks 2, 6, and 10. Study visits will be in line with the Expanded Program of Immunization routine schedule to maximize participation [37]. We will train the research nurse in motivational interviewing techniques, which include reflective listening and expression of acceptance and affirmation. These techniques will enable the research nurse to understand participant’s frame of reference, reinforce participant’s own self-motivational statements, monitor the readiness to change, and affirm the participant’s freedom of choice. Advice will be given with participant’s permission, and when given, the participant will make her own choice. The research nurse will apply these techniques considering the participant’s readiness to change. The interviews will be recorded.

### Usual standard of care

Participants randomized to the usual standard of care group will be counselled by primary healthcare nurses and trained lay counsellors to exclusively breastfeed for the first six months. They will be free to call the clinic staff at any time on their own initiative. Women not receiving motivational interviewing who report adherence concerns during study visits will receive adherence counselling from the primary healthcare nurses and lay counsellors.

All cell phone communications between providers and study participants, in both study arms, will be recorded in a study log.

## Objectives

### Primary objectives

This pilot study will determine the feasibility of conducting a larger trial evaluating the effects of interactive weekly mobile phone text messaging plus motivational interviewing versus usual care in promotion of breastfeeding by HIV-infected women. We will assess the feasibility of the trial for participant recruitment, proportion of eligible participants consenting to participate, and proportion with complete outcome assessment.

### Secondary objectives

To determine if there is a signal of intervention effect on adherence to breastfeeding that may inform larger trial design. We assume text messaging will remind women about the importance of breastfeeding and reinforce regular communication with clinic staff to address adherence related problems. Motivational interviewing may build confidence and motivate women to continue breastfeeding.

## Study endpoints

### Sampling and enrolment

Participants will be enrolled over a period of three months during weekdays.

### Primary endpoints

The primary feasibility outcomes will include the number of participants invited to participate in the study who consent to participate, number of participants with complete evaluation of infant feeding practices at all study visits as assessed by the infant feeding questionnaire, and the number of involuntary disclosures of HIV status due to text messaging. Criteria for feasibility success will include:five participants recruited per week (i.e. 60 participants over 12 weeks);about 75% of all eligible participants consent to participate;complete evaluation of outcomes in at least 70% of all recruited participants;breastfeeding adherence rate of at least 70% in the intervention group, at 24 weeks post delivery;number of participants reporting involuntary disclosure of HIV status due to text messaging less than 5%.

### Secondary endpoints

Secondary outcomes include number of participants who are exclusively breastfeeding 24 weeks post delivery and number of participants who are breastfeeding. This will be assessed using a questionnaire of food items given to the baby in the last 24 h and one week preceding inquiry. Participants will be considered either “adherent” to exclusive breastfeeding if babies receive only breastmilk and no other liquids or solids based foods or “non-adherent” if other foods are given. Breastfeeding will be assessed by self-report of women who report breastfeeding in addition to giving other foods. Study outcomes will be evaluated at weeks 2, 6, 10, and 24.

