### Secondary outcomes

We will follow the Consolidated Standards of Reporting Trials (CONSORT) extension for reporting pilot trials [40]. We will use the intention-to-treat principle for secondary outcome analysis, where all participants randomized will be considered per group assignment. In this analysis, we will impute missing outcome data using both the best-case and worst-case scenario. For adherence outcomes, missing data at study visits will be considered as “adherent” and “non-adherent,” respectively. For breastfeeding outcome, missing data at study visits will be considered as “stopped breastfeeding” and “still breastfeeding.” The study is not adequately powered to test intervention effects and these will be of secondary interest to assess potential trends. Logistic regression models will be built for binary outcomes. For timed endpoints, the cumulative proportions of women stopping exclusively breastfeeding and cumulative proportions of those stopping any breastfeeding, we will use the Kaplan–Meier survival analysis followed by multivariable Cox proportional hazards model to adjust for possible baseline imbalances. We will report odds ratios and hazard ratios (95% CI) as initial estimates of effect. Table 1 provides a summary of methods of analysis for each variable. Separately, we will conduct sub-analysis to assess subgroup effects, a summary of this analysis follows below.

**Table 1 Tab1:** Variables, measures, and methods of analysis

Variable/Outcome	Type	Hypothesis	Outcome measure	Method of analysis
l. Primary				
a. Participants recruited	Count		Percentage recruited	Descriptive statistics
b. Participants consenting	Count		Percentage consenting	Descriptive statistics
c. Completeness of evaluation of outcomes	Count		Percentage with complete outcome evaluation	Descriptive statistics
d. Cumulative breastfeeding adherence at six months	Binary		Percentage adherence in the last 24 h and 1 week	Descriptive statistics
2. Secondary				
a. Adherence to exclusive breastfeeding	Binary	SMS + motivational interview leads to better adherence to breastfeeding than usual care	Percentage adherence in the last 24 h and 1 week	Logistic regression
b. Time to stopping breastfeeding	Time-to-event	SMS + motivational interview prolongs time to stopping breastfeeding than usual care	Reporting of complete cessation of breastfeeding	Kaplan–Meier survival analysis

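### The breastfeeding outcome as worded leaves out exclusive breastfeeders, and the 70% adherence criterion is not tied to one definition

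*Protocol article*

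**What the plan says.** **The two feeding outcomes.** In the protocol article, Secondary endpoints, a woman is adherent to exclusive breastfeeding "if babies receive only breastmilk and no other liquids or solids based foods". The other outcome, breastfeeding, has one operational sentence: "Breastfeeding will be assessed by self-report of women who report breastfeeding in addition to giving other foods".

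The Analysis plan (Secondary outcomes) treats that outcome differently. Missing values are set to stopped or still breastfeeding, the survival analysis concerns the stopping of any breastfeeding, and the time-to-event row of Table 1 is based on complete cessation.

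**The 70% criterion.** It appears in three places:
- Primary endpoints: "breastfeeding adherence rate of at least 70% in the intervention group, at 24 weeks post delivery".
- Abstract, Methods and design: "breastfeeding adherence rates of at least 70% in the intervention group, six months after delivery".
- Table 1, primary row d: "Cumulative breastfeeding adherence at six months", with the outcome measure "Percentage adherence in the last 24 h and 1 week".

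Table 1 has a separate secondary row a, "Adherence to exclusive breastfeeding", with the same outcome measure.

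**The concern.** There are two defects in what is written.

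First, the definition of breastfeeding in Secondary endpoints captures mixed feeders only. The weekly message encourages exclusive breastfeeding (Mobile phone text messaging), so a woman whom the intervention moves from mixed to exclusive feeding would leave the numerator. An analyst who followed the sentence could report an effect in the wrong direction. The Sample size section says that the pilot's effect estimates will feed the main trial's sample size calculation.

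Second, the 70% threshold is one of five criteria for feasibility success, yet its three statements do not say whether the feeding is exclusive or any. One of them adds the word *cumulative*, which does not fit a single time point or a recall of 24 hours and one week. If the reading is chosen after the data are seen, the same data may count as a pass or a fail.

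**Working it through.** **Inputs from the article.** Five women a week for 12 weeks (Primary endpoints); 1:1 allocation (Randomization scheme); threshold 70% in the intervention arm. The feeding counts and true rates below are assumed, because the article does not give the share of mixed feeding.

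**The plan's own figure.** 5 × 12 = 60, which agrees with the stated sample size. With 1:1 allocation each arm has about 60 / 2 = 30. The criterion needs 0.70 × 30 = 21 women.

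**Step 1: the breastfeeding outcome under two readings.** Assumed week-24 counts:

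| | Exclusive | Mixed | Stopped |
|---|---|---|---|
| Intervention (30) | 15 | 9 | 6 |
| Control (30) | 9 | 12 | 9 |

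- Any breastfeeding: (15 + 9)/30 = 24/30 = 80% versus (9 + 12)/30 = 21/30 = 70%. Difference +10 points; odds ratio (24 × 9)/(6 × 21) = 1.71.
- As worded (mixed only): 9/30 = 30% versus 12/30 = 40%. Difference −10 points; odds ratio (9 × 18)/(21 × 12) = 0.64.

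A second assumed set (intervention 15 exclusive, 8 mixed, 7 stopped; control 5, 14, 11) gives 23/30 versus 19/30, odds ratio 1.90, for any breastfeeding, and 8/30 versus 14/30, odds ratio 0.42, as worded. The reversal does not depend on one choice of counts, but its size does.

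**Step 2: the 70% criterion, exclusive or any.** On the first set, the intervention arm passes on any breastfeeding (24 ≥ 21) and fails on exclusive (15 < 21). With any breastfeeding held at 24/30, the exclusive reading fails whenever 20 or fewer of the 24 are exclusive.

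The exact chance of passing is P(X ≥ 21) for X binomial(30, p):

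| True rate p | 50% | 60% | 70% | 75% | 80% |
|---|---|---|---|---|---|
| P(pass) | 0.02 | 0.18 | 0.59 | 0.80 | 0.94 |

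Assumed true rates of 80% any and 50% exclusive therefore pass with probability 0.94 and 0.02 respectively.

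**Step 3: cumulative or week 24.** If *cumulative* means adherent at all four visits (weeks 2, 6, 10 and 24), a per-visit rate q gives q⁴ when visits are independent: 0.75⁴ = 0.32 and 0.90⁴ = 0.66. With full dependence the cumulative rate is simply q. Independence gives a low figure, so for q between 75% and 90% these are ranges (0.32 to 0.75, and 0.66 to 0.90), each spanning the 70% threshold except that the upper range starts just below it. A pass at week 24 can become a fail.

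**The case against.** The strongest reply is that the article, read as a whole, shows what was meant.

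- The sentence on breastfeeding is probably a slip for breastfeeding with or without other foods. The analysis section codes the outcome as stopped or still breastfeeding, and no row of Table 1 tests mixed feeding alone. This stands as evidence of intent. A reader might infer that the trial will report an effect of the wrong sign; the article does not support that. It supports only that the one operational definition is wrong and contradicts the analysis section.
- The only definition of adherent is exclusive, and the analysis section separates adherence outcomes from the breastfeeding outcome. Table 1 rows 1d and 2a could be one variable, described first and then compared between arms. So it would go too far to call the criterion wholly undefined. Yet it is never linked to that definition, and Table 1 gives it a different name from exclusive adherence.
- How two recall windows combine may be left to an analysis plan that is not shown. That is fair, and this is the lesser part of the point.

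Some stronger inferences also fail. The 70% completeness criterion covers all visits in all recruited women, so it does not imply that 9 of 30 intervention women lack a week-24 result. A best-case and worst-case rule for missing adherence data does exist, although it is stated under secondary outcomes. The Background cohort figure on early switching to formula gives no week-24 rate without further assumptions, so it cannot show how likely the criterion is to be met. Nothing says that failing one criterion stops the main trial, and keeping an adherence threshold among the feasibility criteria is a legitimate design choice.

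**Conclusion.** The point holds as a contradiction in stated definitions and should be fixed, though it is not a fundamental flaw. The secondary outcome sentence excludes exclusive breastfeeders and conflicts with the analysis section. The 70% criterion is given at a single time point in two places and as cumulative in a third, without being tied to exclusive or any feeding.

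The consequence can be a change of sign for the secondary outcome (+10 to −10 points in the illustration) and a change from pass to fail for the criterion. Both sizes rest on assumed feeding counts or rates and on about 30 women per arm. No sample size, significance level or power changes, since the article calculates none of these from an effect, and it calls intervention effects of secondary interest.

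**What to change.** 1. In Secondary endpoints, define any breastfeeding as the infant receiving breast milk, with or without other foods.
2. In the Abstract, Primary endpoints and Table 1, state in the same words that the 70% criterion is exclusive breastfeeding, as adherent is already defined, at week 24. Delete *cumulative* from Table 1.
3. Name one recall window as the main one and use the other as a sensitivity analysis.
4. Use all women randomised to the intervention as the denominator. Count missing as non-adherent for the pass/fail decision, and show the best case already described in the analysis section alongside it.

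The cost is wording. The questionnaire already asks about both windows, and Trial status says that recruitment has not begun. The downside is that the criterion becomes harder to meet, because exclusive breastfeeding can be no more common than any breastfeeding and missing women count against it.
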